#### Study arms

Participants allocated to the experimental group receive the written educational program via mail immediately following randomization. Telephone follows-ups are conducted 1 week, 1 month, 6 months and 1 year post-intervention, and last 5 to 10 minutes. Participants in the control ‘wait-list’ group are monitored during the first 6 months following randomization and then receive the same intervention as the experimental group.

### Study outcomes

Outcomes are measured at all study follow-up points. At baseline, questionnaires are completed at the participants’ homes during an interview with the research coordinator. Follow-up is by telephone interview with the same coordinator. Self-reported socio-demographic variables, health status variables and prescription details are collected at baseline.

### Primary outcomes

#### Prescription change rate at 6 months

The primary outcome of the study is cessation of benzodiazepines in the 6 months following receipt of the intervention, ascertained by pharmacy renewal profiles and confirmed by patient self-report. A 1-year follow-up will be undertaken to determine whether change rates are sustained over the long-term. The definition of discontinuation will be an absence of any benzodiazepine prescription renewal at the time of the 6-month follow-up. Dose reductions will also be measured and will be defined as ≥50% reductions in the renewal profile for at least 3 consecutive months beginning at the time of the 6-month follow-up. The discontinuation/dose reduction rate among participants in the experimental arm will be compared to the discontinuation/dose reduction rate among participants in the control arm. In this way we will be able to determine the absolute rate of discontinuation attributable to the intervention. This outcome measure pertains to the individual level.

The 6-month period and 1-year follow-up were chosen because although there is no agreement on the time frame of change, the trans-theoretical model supposes that, typically, once people start thinking about changing their behavior, decision and planning of the action is usually done within the following 6 months. Maintenance of the new behavior begins after 6 months of being in the active stage of changing and continues for at least 6 months [59]. Pharmacy profiles, supplied monthly by fax to the research center by the pharmacist, were chosen to measure prescription change rates because of the high amount of information they contain. Pharmaceutical profiles vary in the information they contain between pharmacies of the same chain depending on the owners. However, vital information to determine change rates, such as the date of renewal, the dose and the quantity of the prescription are always listed. Using this objective measure allows comparison and validation of patient reported outcomes, and thus more accurately and objectively determines the effect of the intervention.

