We expect our intervention to achieve a rate of discontinuation that is at least as great as that achieved in previous studies by medication review by pharmacist and contact with physician (range 19 to 24%, mean 22%) [29,43,63] or by simple discontinuation letters (range 13 to 20%, mean 16%) [47,64-67]. However, it is possible that individuals who do not receive the intervention may have rates of discontinuation as high as 6% for inappropriate prescriptions (range 2 to 6%, mean 4%) [29,43,47,64-66]. Our study will therefore be powered to detect a minimal 20% increase in inappropriate medication discontinuation due to use of the intervention and an absolute minimal rate of discontinuation of 25%. Based on an alpha of 0.05 and 80% power to detect a 20% difference, 58 participants are needed for each group. To detect greater differences, a lower sample size is needed. However, due to the cluster design of this study, adjustments need to be made to account for both clustering and for the effect of the coefficient of variation of the cluster size [68]. Based on current recruitment data (16 clusters, cluster sizes 6 to 27), the coefficient of variation was established at 0.527 using the minimum/maximum cluster size estimation method [68] and estimated intra-cluster correlation set at 0.05. After computing the coefficient by which to multiply our sample size to account for these factors we obtained 1.79 [69]. Current loss to follow-up in the study (in the first 185 recruited participants) was established at 9%. Therefore 114.2 (58 × 1.79 × 1.10 = 114.2) participants will be needed for each group. A sample of 250 individuals will be recruited.

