### Analysis plan

Data will be analyzed using an intention-to-treat approach. Descriptive statistics (means, proportions) will first be calculated to assess the balance between the groups on important confounders, such as age, sex, health status, baseline beliefs about medications and benzodiazepine use. In order to answer the main research question driving this study - whether an educational intervention targeting consumers directly as catalysts for engaging physicians and pharmacists in collaborative discontinuation achieves an inappropriate prescription discontinuation rate of at least 20% compared to usual care - we will use a marginal model estimated via generalized estimating equations (GEE) with a binary outcome and an identity link, with an exchangeable correlation structure to account for correlation between participants in the same cluster [69]. Risk differences between the control and experimental groups will be calculated and the robust variance estimator will be used to estimate the associated 95% confidence interval (CI) and *P* value [70]. As a sensitivity analysis (and/or if any confounders are unbalanced between the groups), we will estimate the risk difference for the intervention via a marginal model estimated via GEE with an exchangeable correlation structure. The robust variance estimator will again be used. In secondary analyses, we will calculate risk differences in subgroups of interest (for example, very older people, women, baseline beliefs about medication and degree of polypharmacy). The analysis will be carried out at both the cluster and individual levels.

In order to determine whether the patient intervention altered beliefs about the necessity-concern ratio, knowledge or risk perception for the inappropriate prescriptions, as well as self-efficacy, paired t-tests will be used to evaluate change scores pre- and post-intervention. The potential of the intervention to engage participants in preventive health behaviors will be evaluated via chi-square tests comparing intervention and control groups. These analyses will be carried out at the individual level.

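### Cessation is scored from no renewal at the 6-month point, without a window, a supply rule or a rule for conflict with self-report, so some continuing users can meet it

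*Protocol article*

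**What the plan says.** All of the endpoint text stands in the protocol article under Prescription change rate at 6 months.

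- **Outcome and sources.** The outcome is benzodiazepine cessation over the 6 months after the brochure, "ascertained by pharmacy renewal profiles and confirmed by patient self-report".
- **Working definition.** "The definition of discontinuation will be an absence of any benzodiazepine prescription renewal at the time of the 6-month follow-up".
- **Dose reduction.** It is defined as "≥50% reductions in the renewal profile for at least 3 consecutive months beginning at the time of the 6-month follow-up".
- **Data held.** "Pharmacy profiles, supplied monthly by fax to the research center by the pharmacist" are the source. Their content varies between pharmacies, but "the date of renewal, the dose and the quantity of the prescription are always listed".
- **Standing of the two sources.** Of the pharmacy record the article says: "Using this objective measure allows comparison and validation of patient reported outcomes".

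Other sections bear on the point. Components of the intervention describes a 21-week tapering programme. Study arms schedules a telephone call at 6 months and gives controls the brochure after their first 6 months. Sample size puts loss to follow-up at 9%.

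**The concern.** The rule scores success from the absence of an event at one moment. Whether a renewal falls at that moment depends on when the last fill was made and how much was dispensed, as well as on whether the participant still takes the drug. Two kinds of continuing user can therefore satisfy the sentence: one whose earlier fill runs past month 6, and one who has moved to another pharmacy.

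The article's own text shows the gap. Partial reduction needs 3 consecutive months, while full cessation, the stronger claim, needs no duration. The outcome is also described first as something that happens over 6 months and then as a state at one time point. These are different measures.

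This is not detail that an article would leave to an analysis plan, because the article states the operational definition itself. Misclassified continuing users raise the observed rate in both arms, shrink the risk difference and cost power. If refill timing differed between arms, for instance because tapering participants refill more slowly, the estimate could be biased in either direction.

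**Working it through.** **1. The plan's own figures.** Sample size states 58 per group for a 20-point difference, a 25% intervention rate (so 5% in controls), alpha 0.05 and 80% power. The two-proportion formula with pooled variance, two-sided, gives 48.8, rounded up to 49. With continuity correction it gives 58.4, which is 58 or 59 depending on rounding. The stated 58 therefore reproduces with the correction. The inflation 58 × 1.79 × 1.10 = 114.2 also reproduces. This point does not dispute those figures.

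**2. Inputs for the illustration.**
- True cessation 5% v 25% (Sample size).
- 250 participants allocated 1:1, so 125 per arm (Sample size; Design).
- 9% loss and cluster multiplier 1.79, both as stated (Sample size).
- Effective number per arm: n = 125 × 0.91 / 1.79 = 113.75 / 1.79 = 63.5.
- f, the fraction of continuing users wrongly scored as stopped, equal in both arms. **This is an assumption.** The documents give no refill interval, supply length or misclassification rate, so a range is shown.

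**3. Formulas.** The observed rate is p′ = p + f(1 − p), so the observed difference is 0.20 × (1 − f). Power, without continuity correction, is Φ[(d√n − 1.96√(2p̄(1 − p̄))) / √(p₁(1 − p₁) + p₂(1 − p₂))]. Here p₁ and p₂ are the observed rates, d is their difference and p̄ their mean.

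**4. Results.**

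| f | Control | Intervention | Difference (points) | Power |
|---|---|---|---|---|
| 0 | 5.0% | 25.0% | 20.0 | 0.89 |
| 2% | 6.9% | 26.5% | 19.6 | 0.85 |
| 5% | 9.75% | 28.75% | 19.0 | 0.78 |
| 10% | 14.5% | 32.5% | 18.0 | 0.67 |
| 20% | 24.0% | 40.0% | 16.0 | 0.49 |

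Worked line for f = 5%: control 0.05 + 0.05 × 0.95 = 0.0975; intervention 0.25 + 0.05 × 0.75 = 0.2875; d = 0.19; p̄ = 0.1925. The numerator is 0.19 × √63.5 − 1.96 × 0.5576 = 0.422 and the denominator is 0.5411. The ratio is 0.78, and Φ(0.78) = 0.78.

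Most of the loss comes from the higher variance at the raised rates; the shrinkage of the difference is small by comparison. An f of about 5% is enough to bring power just under the planned 80%.

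**5. Where a window can lie.** Six months is about 26 weeks, and 26 − 21 = 5 weeks. A participant who starts the taper at once finishes about 5 weeks before the assessment, and later if the start is delayed. A look-back on dispensing longer than that overlaps the taper and could score a participant who finished in time as not stopped. A window running forward from month 6, like the one for dose reduction, fails for another reason: controls receive the brochure at that point.

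**The case against.** The strongest reply is that the endpoint has two parts. Cessation must also be confirmed by the participant, the 6-month call is scheduled, and Table 1 lists a tapering questionnaire at that visit. A participant who is reached and says that tablets are still being taken, or are filled elsewhere, would not be confirmed as stopped. Much of this stands. It means that holding leftover tablets does not automatically produce a false success, and that the larger values of f would require confirmation to fail widely. It does not close the gap, because the defining sentence omits confirmation, no rule settles a disagreement, and the article treats the pharmacy record as the check on self-report. If the record prevails, the error stays.

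A reader might go further and infer that participants who die, move or are lost are scored as stopped, since they too have no renewal. The documents do not support that. "Data will be analyzed using an intention-to-treat approach" settles analysis by allocated arm and says nothing about how a missing outcome is filled. A cessation that must be confirmed is not met by someone who cannot confirm it. The 1.10 inflation for loss also suggests that lost participants contribute no outcome. No bias figure should be built on that inference.

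It is also fair to say that the difference in duration between the two definitions is not a contradiction. A reduction needs a run of months to be told apart from irregular refilling, and the 1-year follow-up addresses whether change is sustained. The contrast shows only that the authors recognised the need for a duration in one case and gave none in the other.

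**Conclusion.** The point holds as a weakness in a definition that the article itself fixes. The primary endpoint has no window, no supply rule and no rule for discordant sources, so a continuing user can meet it as worded. The data for a better rule are already collected.

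The size cannot be derived from the documents. Under equal misclassification in both arms, 5% v 25% and 63.5 effective participants per arm, power runs from 0.89 with no error to 0.78 at 5% and 0.49 at 20%; the upper values are not forecasts. Equal misclassification pulls the risk difference toward zero and does not create a false positive. Bias in either direction would need the error to differ by arm, and the documents give no basis for putting a number on that. The sponsor should correct the definition; the sample size calculation is not called into question.

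**What to change.** 1. **Supply rule.** Define cessation from the recorded dispensing date and quantity: no benzodiazepine supply covers the 6-month date. This deals with long fills, which a short look-back on dispensing alone would miss.
2. **Window.** Add a fixed period without dispensing that ends at month 6 and is identical in both arms. Keep it short enough not to reclassify participants who completed the 21-week programme in time, which means no more than about 5 weeks. Do not run it forward.
3. **Two sources.** Require self-report to agree, and score discordant cases as not stopped. Self-report is the only check on fills at another pharmacy. Report the number of discordant cases by arm.
4. **Secondary point.** Score participants with neither a profile nor a self-report as not stopped, with a complete-case sensitivity analysis.

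**Cost.** Endpoint wording, and re-derivation from profiles already faxed monthly; no new data collection. Observed cessation rates may fall somewhat. Some misclassification will remain, because a participant who tapered and stopped may hold leftover tablets that appear as supply covering month 6.

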**Methods/Design:**

This is a cluster randomized controlled trial using a two-arm parallel-design. A total of 250 older chronic benzodiazepine users recruited from community pharmacies in the greater Montreal area will be studied with informed consent. A participating pharmacy with recruited participants represents a cluster, the unit of randomization. For every four pharmacies recruited, a simple 2:2 randomization is used to allocate clusters into intervention and control arms. Participants will be followed for 1 year. Within the intervention clusters, participants will receive a novel educational intervention detailing risks and safe alternatives to their current potentially inappropriate medication, while the control group will be wait-listed for the intervention for 6 months and receive usual care during that time period. The primary outcome is the rate of change in benzodiazepine use at 6 months. Secondary outcomes are changes in risk perception, self-efficacy for discontinuing benzodiazepines, and activation of patients initiating discussions with their physician or pharmacist about safer prescribing practices. An intention-to-treat analysis will be followed.

The rate of change of benzodiazepine use will be compared between intervention and control groups at the individual level at the 6-month follow-up. Risk differences between the control and experimental groups will be calculated, and the robust variance estimator will be used to estimate the associated 95% confidence interval (CI). As a sensitivity analysis (and/or if any confounders are unbalanced between the groups), we will estimate the risk difference for the intervention via a marginal model estimated via generalized estimating equations with an exchangeable correlation structure.

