### The educational intervention

The educational intervention consists of a seven-page letter-size paper brochure developed specifically for this trial. The language for the intervention is set at a grade six reading level and written in 14 point font to facilitate accessibility of the material. The brochure is mailed to the intervention group within 1 week of group allocation. The control/wait-list group receives the educational tool 6 months later. As the intervention is sent individually to participants and participants within each cluster are unknown to one another, the intervention only pertains to the individual participant.

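### Dose reduction is judged over three months that start when wait-list controls are sent the brochure, so this component has no usual-care comparator

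*Protocol article*

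**What the plan says.** Four parts of the protocol article bear on this point.

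- **Prescription change rate at 6 months.** Discontinuation is "an absence of any benzodiazepine prescription renewal at the time of the 6-month follow-up". Dose reduction is also measured, as "≥50% reductions in the renewal profile for at least 3 consecutive months beginning at the time of the 6-month follow-up". The section then plans a between-arm comparison: "The discontinuation/dose reduction rate among participants in the experimental arm will be compared to the discontinuation/dose reduction rate among participants in the control arm". The next sentence uses that comparison to obtain the rate attributable to the intervention.
- **The educational intervention.** "The brochure is mailed to the intervention group within 1 week of group allocation". For the other arm: "The control/wait-list group receives the educational tool 6 months later".
- **Study arms.** Controls "are monitored during the first 6 months following randomization and then receive the same intervention as the experimental group".
- **Abstract, Methods/Design.** It states that "the control group will be wait-listed for the intervention for 6 months and receive usual care during that time period".

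The article neither holds back the control mailing until the dose-reduction window has closed nor restricts the control arm's window to months before its brochure.

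**The concern.** A between-arm difference measures the effect of the brochure only if one arm has not had it while the outcome is observed. The wait-list design provides that contrast for six months. The dose-reduction window opens as those six months end, so both arms hold the brochure for practically the whole of it.

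At stake is the dose-reduction comparison and the combined rate built on it. The article places that combined comparison under its primary outcome heading and draws an attributable effect from it, so it is not merely descriptive. A control whose reduction lasts because of the brochure would be counted as a usual-care reduction, which would shrink the apparent effect.

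**Working it through.** **1. The plan's own figure, to see what depends on this window.** The Sample size section states: "Based on an alpha of 0.05 and 80% power to detect a 20% difference, 58 participants are needed for each group". It gives 25% as the minimum intervention-arm rate, so the implied control rate is 25% − 20% = 5%. With two-sided alpha 0.05 (sidedness is not stated), 80% power and a mean proportion of 0.15:

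- n = [1.96·√(2·0.15·0.85) + 0.842·√(0.05·0.95 + 0.25·0.75)]² / 0.20² = (0.990 + 0.408)² / 0.04 ≈ 48.8, or 49 per group.
- With continuity correction: (48.8/4)·[1 + √(1 + 4/(48.8·0.20))]² ≈ 58.4, which agrees with the stated 58.
- Inflation: 58 × 1.79 × 1.10 = 114.2 per group, as stated.

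Every rate in this calculation is a discontinuation rate. No dose-reduction rate enters, so the sample size and its power do not depend on the dose-reduction window.

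**2. The timeline, from randomization.**

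| Period | Intervention arm | Control arm | Outcome judged |
|---|---|---|---|
| Month 0 to 6 | Brochure in hand from about week 1 | Usual care | – |
| Month 6 | Brochure in hand | Brochure sent | Discontinuation |
| Month 6 to 9 (at least) | Brochure in hand | Brochure in hand | Dose reduction |

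The six-month delay could run from allocation or from the intervention-arm mailing. These differ by at most one week. Three months is about 13 weeks, so on the scheduled dates at most about 1/13 (8%) of the control window precedes the control mailing.

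**3. Does another time origin help?** The section on the primary outcome counts six months from receipt of the intervention, and Table 1, which covers both arms, labels its follow-up columns as post-intervention. If a control's six months ran from that person's own brochure, the window would open six months after exposure. If they ran from randomization, it opens at exposure. Neither leaves the control window unexposed.

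**4. Which controls could be misclassified?**

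| Control participant | Counted as reduced? | Due to the brochure? |
|---|---|---|
| At least 50% down at month 6, would have stayed down anyway | Yes | No |
| At least 50% down at month 6, stays down because of the brochure | Yes | Yes |
| First renewal in the window follows the mailing and is reduced | Possibly, depending on how renewals are assigned to months | Possibly |
| Starts reducing weeks after the mailing | No, on the literal wording | Yes, but not counted |

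The second and third rows can only add control reductions.

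**5. Size.** Let *b* be the proportion of controls counted as reduced only because of the brochure. Then observed difference = true difference − *b*, with *b* ≥ 0. The article gives neither *b* nor any dose-reduction rate in either arm, so the direction follows but no value does.

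**The case against.** The strongest reply is that the definition largely protects itself. Read literally, the reduction must begin at the 6-month follow-up, so a control must already be at least 50% down when the window opens. A brochure mailed at that moment has to arrive, it tells the reader to consult a doctor or pharmacist before stopping, and it offers a 21-week taper. A reduction that starts some weeks later does not qualify. This stands, and it makes *b* smaller. It does not make it zero: persistence over the three months is still observed under exposure, and the first renewal in the window may fall after the mailing.

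The second reply is that the primary outcome is cessation. This also stands. The primary objective, the sample-size question and the main question of the Analysis plan all concern discontinuation.

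Three stronger inferences are tempting, and the article does not support them.

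- **That the trial loses power for its main question.** Applying contamination to the 5% and 25% planning rates would suggest this, but those are discontinuation rates, and discontinuation is judged at month 6, outside the exposed window.
- **That every control who responds promptly to the brochure is counted as a control-arm reduction.** The literal wording excludes most of them.
- **That the problem is beyond repair at analysis.** The pharmacy profiles are supplied monthly and always list the renewal date, dose and quantity, so a comparison limited to the period before month 6 can be made.

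**Conclusion.** The point holds for the dose-reduction component and for the combined discontinuation/dose reduction comparison. As written, neither is a comparison with usual care, because the control arm's dose-reduction status is determined almost entirely after its scheduled brochure. Complete discontinuation at month 6 is unaffected, and so are the stated sample size and power.

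The expected bias is toward no difference. Its size is unknown, and it is probably limited if the reduction must already be present at month 6. The conclusion rests on two assumptions: that the control mailing follows the stated schedule, and that the brochure does not lead controls to increase their use.

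**What to change.** For the between-arm comparison, define dose reduction in both arms, timed from randomization, as a reduction of at least 50% from the pre-randomization renewal profile. Judge it over a fixed window that ends at the 6-month follow-up and before the control brochure is mailed, for example the three months ending at month 6. Use the same definition in the combined rate. Report persistence over months 6 to 9 for the intervention arm only, as description. Align the sections on the primary outcome, the educational intervention and the study arms with this wording.

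No new data are needed. The Trial status section puts the trial at about 80% complete, so the wording should be settled before outcomes are compared by arm; a later change could look data-driven.

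The cost is that reductions starting shortly before month 6 will not meet a three-month requirement in the between-arm comparison. Some late responders in the intervention arm would therefore be visible only in the descriptive follow-up.

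### The primary outcome is named as cessation, but the stated between-arm comparison adds dose reduction and the abstract names an undefined rate of change; only cessation is powered

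*Protocol article*

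**What the plan says.** Three descriptions of the primary outcome appear in the protocol article.

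- **Cessation.** The section on prescription change rate at 6 months opens with "The primary outcome of the study is cessation of benzodiazepines in the 6 months following receipt of the intervention". The same sentence goes on to require pharmacy renewal records backed by the patient's own report. The operative definition that follows is "The definition of discontinuation will be an absence of any benzodiazepine prescription renewal at the time of the 6-month follow-up"; it does not repeat the self-report requirement.
- **Discontinuation together with dose reduction.** A few lines later, still under the heading for primary outcomes, the comparison between arms is given as "The discontinuation/dose reduction rate among participants in the experimental arm will be compared to the discontinuation/dose reduction rate among participants in the control arm". Dose reduction is defined as "≥50% reductions in the renewal profile for at least 3 consecutive months beginning at the time of the 6-month follow-up". The next sentence says that this comparison will give the absolute discontinuation rate attributable to the intervention.
- **Rate of change.** The abstract states "The primary outcome is the rate of change in benzodiazepine use at 6 months" and then "The rate of change of benzodiazepine use will be compared between intervention and control groups at the individual level". No definition of this rate is given.

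Elsewhere only discontinuation appears. The study objectives measure effectiveness by it. The sample size section says "Our study will therefore be powered to detect a minimal 20% increase in inappropriate medication discontinuation due to use of the intervention" and uses discontinuation rates throughout. The main question in the analysis plan also names discontinuation alone. Dose reduction is not listed among the secondary outcomes.

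**The concern.** The sentence that describes the comparison does not match the sentence that names the outcome. The slash could mean a composite or two separate endpoints, and nothing in the text settles which. Dose reduction appears only in the primary-outcome section, so its status is open.

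Three things are at stake. First, a reader of the final report could not tell which result was meant to be primary, and the more favourable one could be chosen after the results are known. Second, the comparison as written has no planning basis, because no dose-reduction rate is given for either arm. Third, the dose-reduction component is observed after the control arm has been given the intervention.

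**Working it through.** **1. Which outcome was powered.** Inputs from the sample size section: intervention rate 25%, difference 20 points (hence control 5%), alpha 0.05, power 80%. Two-sided testing is assumed, since sidedness is not stated.

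n = [1.96 × √(2 × 0.15 × 0.85) + 0.8416 × √(0.05 × 0.95 + 0.25 × 0.75)]² / 0.20² = (0.990 + 0.408)² / 0.04 = 48.8

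With continuity correction: (48.8 / 4) × [1 + √(1 + 4 / (48.8 × 0.20))]² = 58.4

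This matches the stated 58. The inflation also reproduces: 58 × 1.79 × 1.10 = 114.2. Every input is a discontinuation rate, so cessation is the powered outcome and its sample size is sound on its own terms.

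**2. What the composite would do to power.** With 250 recruited at 50:50, 9% lost and the stated inflation factor, the effective size is 125 × 0.91 / 1.79 = 63.5 per arm. Power (pooled test, no continuity correction) is

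Φ{[d√n − 1.96√(2p̄(1 − p̄))] / √(p₁(1 − p₁) + p₂(1 − p₂))}

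| Control v intervention | Power |
|---|---|
| 5% v 25% (cessation, as planned) | 89% |
| 10% v 30% | 81% |
| 15% v 35% | 75% |
| 20% v 40% | 70% |
| 10% v 35% | 93% |
| 15% v 40% | 89% |

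All rows but the first are assumptions. Power for the composite may be lower or higher than planned; the documents do not allow it to be fixed.

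**3. False-positive risk if either version may be claimed.** Ceasers are a subset of those who cease or reduce. With null cessation rate c and null rate r of dose reduction alone, the two test statistics correlate at √[c(1 − c − r) / ((1 − c)(c + r))]. Taking c = 5% from the planning values and assuming r, with each test two-sided at 0.05:

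| Assumed r | Correlation | Either significant, simulated (64 per arm) | Either significant, bivariate normal |
|---|---|---|---|
| 5% | 0.69 | 8.3% | 8.4% |
| 10% | 0.55 | 8.5% | 8.9% |
| 15% | 0.46 | 8.8% | 9.2% |

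Two independent tests would give 1 − 0.95² = 9.75%, so the range is 8 to 9%.

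**4. Whether the comparison can deliver its stated purpose.** A combined rate equals the rate of ceasers plus the rate of those who only reduce. Its between-arm difference equals the discontinuation difference only if reduction alone is equally common in both arms, which cannot be presumed.

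**5. Timing.** The educational intervention and study arms sections give controls the brochure at 6 months. The dose-reduction window starts at the 6-month follow-up and lasts at least three months. The observation period for that component therefore falls after controls are exposed.

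**The case against.** The strongest reply is that cessation is plainly the intended primary outcome. The only sentence in the body that names a primary outcome names cessation; the objectives, sample size and analysis plan agree; dose reductions are introduced as something also measured; and the abstract's rate is analysed by risk differences, so it is probably a loose label for a binary cessation outcome. This largely stands. It makes cessation the obvious default and leaves two definable candidates, not three. It does not remove the sentence that specifies a different comparison under the primary heading.

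Three stronger readings are tempting, and the documents do not support them.

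- A reader might infer that several primary results are to be tested under one alpha. No co-primaries are declared, so the 8 to 9% applies only if both versions can be claimed.
- A reader might infer from the one-sentence definition that anyone who disappears from the pharmacy record counts as having stopped. The outcome sentence requires confirmation by the patient, and the sample size is inflated for loss, which treats those lost as not contributing. Scoring them as ceased is not a stated rule. How missing records are handled is detail that a full protocol or analysis plan commonly holds.
- A reader might infer that controls have no defined 6-month window, because the clock is tied to receipt of the brochure. The study arms section has controls monitored for 6 months from randomization, and the brochure is mailed to the intervention arm within a week of allocation. The wording is loose, but the period is given.

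**Conclusion.** The inconsistency is real and concerns the primary outcome itself. Followed literally, the comparison sentence would bring into the primary result a component that was not powered and that is observed after controls receive the intervention. It would also not produce the discontinuation rate it is meant to produce.

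The size of the problem is conditional. If cessation and the composite could each be claimed at 0.05, the chance of at least one false positive is about 8 to 9%, resting on a 5% null cessation rate and assumed null dose-reduction rates of 5 to 15%. With cessation as the single primary outcome, alpha stays at 0.05, 58 and 114.2 per group stand, and power at 250 recruited is about 89% on the stated inflation and loss. The sample size is not in error. Recruitment was about 80% complete at publication, so the wording should be settled before any outcome data are compared by arm.

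**What to change.** In the abstract and in the section on prescription change rate at 6 months:

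1. Name one primary outcome: complete cessation at 6 months from randomization in both arms, ascertained from the pharmacy profile and confirmed by self-report. Repeat the confirmation in the definition of discontinuation.
2. Rewrite the comparison sentence so that it compares discontinuation rates only.
3. List dose reduction, and any composite with cessation, as secondary outcomes. Base any between-arm comparison of them on months before controls receive the brochure.
4. Delete the rate of change from the abstract, or define it there as cessation.

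The objectives, sample size and analysis plan already refer to discontinuation and need no change on this point.

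The cost is a wording change and no extra participants. The sponsor gives up the composite as a fallback primary result. Moving the dose-reduction window earlier may also miss some participants who are still tapering, since the brochure's programme runs 21 weeks. Keeping both outcomes as primary would need an alpha split. At 0.025 cessation would retain about 83% power, but the composite would still lack planning rates and, as now defined, a clean comparison window.
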